### Interventions

#### Psychosocial intervention based on cognitive behavioral therapy methods

Weekly individual sessions of 40 to 50 minutes in duration will be performed in a properly equipped room for the reception and accommodation of participants. The care protocol that was developed for the present study was based on the method of structuring sessions as proposed by Beck [24] and was adapted from a previous study [25]. The psychosocial intervention is described in detail in Table 1.

**Table 1 Tab1:** **Detailed structured psychosocial and educational intervention**

**Weekly**	**Planned activities**
1	• Introduction of the therapist/patient and establishment of rapport
	• Objective measurement of depression and anxiety symptoms
	• Psychoeducation: disease - explanation of the cancer diagnosis and current health status; symptoms - a discussion of uncomfortable symptoms secondary to the cancer; adverse events - an explanation of adverse events that result from treatment procedures; PC - What is it? What is it for? For whom is it provided? When is it provided? How is it provided? Where is it provided?
	• Delivery of the ‘Educational Booklet’ that was developed specifically for this study^1^
	• Establishment of therapeutic goals
	• ‘Partnership Agreement’ - the moment when the therapist and the patient sign a commitment to walk together on the path that will be traveled by both during the five proposed sessions
	• Establishment of the dates and times of the sessions
	• Session summary and feedback
2	• Assessment of weekly progress and a bridge to the previous session
	• Objective measurement of depression and anxiety symptoms
	• Reinforcement of the therapeutic goals that were set in the previous session
	• Early PC - description of the benefits of simultaneous monitoring by a PC team for advanced cancer patients who are submitted to palliative chemotherapy and presentation of the explanatory figure ‘Goals of Care’ [35]
	• Delivery of the Coping Card^2^
	• Session summary and feedback
3	• Assessment of weekly progress and a bridge to the previous session
	• Objective measurement of depression and anxiety symptoms
	• Anxiety mechanisms: perceived symptoms and how to monitor these symptoms
	• Relaxing training - image association
	• Session summary and feedback
4	• Assessment of weekly progress and a bridge to the previous session
	• Objective measurement of depression and anxiety symptoms
	• Mechanisms of depressive symptoms: perceived symptoms and how to monitor these symptoms
	• Identification of automatic thoughts (thought > emotion > behavior), explanation of how thoughts affect emotions and therefore behaviors, and elucidating the key role of thought on emotion and behavior
	• Patient preparation for discontinuation following the next session
	• Delivery of the Coping Card1
	• Session summary and feedback
5	• Assessment of weekly progress
	• Objective measurement of depression and anxiety symptoms
	• Retrospective of the methods used in the previous sessions, including progress, difficulties, commitment, and learning
	• Discussion of the patient’s ability to control and understand the process as a way to prevent serious symptoms
	• General feedback

^1^The Educational Booklet contains practical information in layman’s terms about the possible symptoms secondary to chemotherapy treatment and symptoms that are often associated with advanced cancer. This booklet explains the importance of the clinical support that is provided by teams that specialize in palliative care.

^2^The Coping Cards were prepared using stimulating sentences, and guidelines will be provided during the sessions regarding the appropriate moments when the cards should be read or remembered.

#### Early palliative care

The Palliative Care Unit of BCH offers an outpatient clinic and an inpatient ward with 52 beds that are dedicated to cancer patients who are receiving PC. Six PC doctors were asked to participate in this study and have received training. The Palliative Care Unit includes a medical team and a multidisciplinary team of nurses, nurse assistants, nutritionists, physical therapists, psychologists, speech therapists, occupational therapists, music therapists, dentists, and social workers. An evaluation of the research participants by members of the multidisciplinary team may be requested according to the evaluation by the primary physician of the study.

All of the patients will be evaluated by PC physicians every 3 ± 1 weeks, and the first appointment should occur 2 to 3 weeks after randomization. Therefore, the first PC appointment will occur after the first two sessions of the psychosocial and educational intervention for participants who are allocated to Arm A. The appointments will follow a standard care protocol, which shall be duly recorded in medical records using a standardized protocol for filling out the forms.

The participants in Arm C may receive a routine PC evaluation depending on the indication from the attending oncologist. The patients in Arms A and B who have not undergone at least one session of PC and the patients in Arm A who have not participated in the first two sessions of the psychosocial and educational intervention will be excluded from the statistical analyses.

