Despite evidence of the positive impact of early PC on the progress of cancer patients, PC is often provided to patients at later stages even at oncology and PC reference centers [9]. In Brazil, reliable information on how and when cancer patients are referred to PC is lacking; however, we believe that patients are referred late to PC. The inadequate awareness and stigmatization of PC, which is perceived as a place to die, are barriers that complicate the early referral of patients to PC [10,11]. The title ‘Palliative Care’, which implies improvisation or something provisional, has complicated patient acceptance of PC within the context of early cancer support during chemotherapy. Patients who are referred to PC are often anxious at the first appointment [12], which leads to a high absenteeism rate.

Therefore, the main hypothesis of the present study is that patients with advanced cancer may benefit from a psychosocial and educational strategy that adequately prepares them for initial PC appointments after an early referral to PC.

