## Methods/design

### Main objectives

The main objectives of this study are as follows:To assess the feasibility of a brief psychosocial intervention based on cognitive behavioral therapy (CBT) and early PC in advanced cancer patients, including patient acceptance and satisfaction.To assess the impact of the intervention on symptoms of depression at 90 days after randomization and to compare the differences between the intervention groups and the control group and between the intervention groups.

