### Data collection and randomization

The psychological intervention will be conducted by psychologists trained for the study. Data collection will be conducted by a team of research coordinators from the Center for Research Support at Barretos Cancer Hospital (BCH; Barretos, SP, Brazil).

A trained member of the Center for Research Support, not involved in data collection or statistical analysis, was assigned to handle the randomization process, using tables of random numbers. The study participants will be randomized (1:1:1) into arms A, B or C. Randomization will be based on blocks of six patients and will be stratified as follows: breast, gynecological, gastrointestinal, urological, head and neck, and thoracic. The study arms will be as follows:Arm A (experimental): psychosocial plus early PC, including five weekly psychosocial interventions based on CBT plus early PC (a first medical consult at the Palliative Care Service will be scheduled for 2 to 3 weeks from the study inclusion date and every 3 to 4 weeks thereafter).Arm B (experimental): early PC (a first medical consult at the Palliative Care Service will be scheduled for 2 to 3 weeks from the study inclusion date and every 3 to 4 weeks thereafter).Arm C (no intervention): standard oncologic care.

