### Primary outcome measures

The primary outcome measures are listed below:Descriptive results about the feasibility of the interventions (the average duration of each intervention session in minutes, the number of absences and the reasons for non-attendance in the intervention groups, the accrual rate, and the reasons for ineligibility).Changes in satisfaction with care from baseline according to the FAMCARE-Patient scale at days 45, 90, 120 and 180.Changes in depression symptoms from baseline according to the HADS-D and PHQ-9 at day 90.

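### Randomised patients are excluded from the analyses for non-attendance in Arms A and B only, and more strictly in A than in B, so no planned contrast compares the groups as randomised

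*Protocol article*

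**What the plan says.** Allocation is equal across three arms: "The study participants will be randomized (1:1:1) into arms A, B or C" (Data collection and randomization).

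The last paragraph of Early palliative care then sets attendance conditions for being analysed:

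- **Arms A and B:** the rule removes "The patients in Arms A and B who have not undergone at least one session of PC".
- **Arm A in addition:** it removes those "who have not participated in the first two sessions of the psychosocial and educational intervention will be excluded from the statistical analyses".
- **Arm C:** no attendance condition. "The participants in Arm C may receive a routine PC evaluation depending on the indication from the attending oncologist".

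The rule exempts no outcome. Statistical analysis does not confine it to a secondary or per-protocol analysis, and the article names no all-randomised analysis beside it.

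Two other places bear on the rule. Main objectives asks for the feasibility of the psychosocial intervention and "early PC in advanced cancer patients, including patient acceptance and satisfaction". Primary outcome measures counts "the number of absences and the reasons for non-attendance in the intervention groups" among the descriptive feasibility results, next to change in FAMCARE-Patient and change in HADS-D and PHQ-9 at day 90.

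**The concern.** Randomisation makes the three arms comparable on the day of allocation. This rule then selects patients on what they do over the following weeks, and selects differently in each arm: two conditions in A, one in B, none in C. A patient who declines to attend is lost from A or B, while a similar patient in C stays in.

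The article gives reason to think that the selection is not neutral. Background states: "Patients who are referred to PC are often anxious at the first appointment [12], which leads to a high absenteeism rate". The Discussion expects stigma about the PC unit and psychological approaches to hamper enrolment. Patients who stay away may thus differ emotionally from those who come, in a trial that measures depression, anxiety and satisfaction.

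What is at stake is mainly the effect size. Sample size calculation and the Discussion say that the trial is to estimate magnitude for a later phase III trial, and a selection effect goes straight into that estimate. The interim rule, which acts on an A versus B effect below 0.2, is exposed in the same way.

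**Working it through.** **1. The plan's own figure.** Inputs from Sample size calculation: d = 0.65, two-sided α = 5%, power 80%, two independent means. The noncentral t gives power 79.9% with 38 per arm and 80.9% with 39. The stated 39 per arm is reproduced, so the point does not rest on an error there.

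**2. Which contrasts are affected.**

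| Contrast | Attendance conditions compared |
|---|---|
| A versus C | PC visit and first two sessions, against none |
| B versus C | PC visit, against none |
| A+B versus C | mixed, against none |
| A versus B, including interim | PC visit and first two sessions, against PC visit |

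No row has equal conditions on both sides.

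**3. Size of the bias.** The article gives no non-attendance rate, so f and g are assumptions. Let f be the share of an experimental arm excluded and g the number of SDs by which those patients' outcome would be worse than that of the patients kept. The full arm's mean is then f × g SD worse than the mean of those kept. Exclusion on one side shifts the contrast by

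bias = f × g.

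**4. Type I error.** Take 50 per arm with 25% loss, the lower end of the stated range: 50 × 0.75 = 37.5 per arm. Arm C is set at 37 and the experimental arm at 37.5 × (1 − f), rounded. With no true effect, the rejection rate of the two-sided 5% t test follows from the noncentral t with noncentrality f × g × √(n₁n₂/(n₁+n₂)). For A+B, the same f is assumed in both arms. Example for f = 25%, g = 0.8: 0.20 × √(28 × 37/65) = 0.80.

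| f | g | Bias (SD) | Share of 0.65 | A v C: n, type I error | A+B v C: n, type I error |
|---|---|---|---|---|---|
| 10% | 0.25 | 0.025 | 4% | 34 v 37, 5.1% | 68 v 37, 5.2% |
| 10% | 0.5 | 0.05 | 8% | 34 v 37, 5.5% | 68 v 37, 5.7% |
| 20% | 0.5 | 0.10 | 15% | 30 v 37, 6.9% | 60 v 37, 7.6% |
| 25% | 0.8 | 0.20 | 31% | 28 v 37, 12.3% | 56 v 37, 15.4% |

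**5. A versus B.** Only the difference between the two arms' shifts matters here. If the extra Arm A condition alone removed a further 20% with g = 0.5, the shift would be 0.10 SD, half of the interim threshold of 0.2. The direction is less clear than against C: if the sessions do prepare patients for PC, B could lose more patients at the PC visit than A.

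**6. Against the primary outcomes.** Taken literally, a patient who never attends is both a required observation (absences and their reasons) and an excluded one. On any reading, that patient is missing from the FAMCARE-Patient, HADS-D and PHQ-9 comparisons.

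**The case against.** The strongest reply accepts the text of the rule and contests what is drawn from it. Much of it stands.

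- **Direction.** A reader might infer that the comparisons are biased in favour of the intervention. The article does not show this. Background says that referred patients are often anxious and that absenteeism follows; it does not compare attenders with non-attenders, and it concerns anxiety rather than depression. Some non-attenders may be well patients who see no need for PC. A bias towards the intervention is plausible, no more.
- **Early deaths.** A reader might add that patients who die in the first weeks disappear from A and B but stay in C. They have no day-90 score in any arm, and eligibility requires a life expectancy above 6 months. Refusal and non-attendance carry the point.
- **Feasibility.** A reader might infer that acceptance will be overstated. The feasibility outcomes are called descriptive, and they include accrual and reasons for ineligibility, which reach beyond any analysed set. The rule may be meant only for the between-arm comparisons. The article does not say so, but the conflict exists only on the literal reading.
- **Sample size.** A reader might say that the exclusions were not budgeted. The 25% to 30% monitoring loss is undefined and may already include non-attenders. If the exclusions do come on top, power at d = 0.65 falls from 79.3% (37.5 per arm) to 77.1% or 74.4% when 10% or 20% of one experimental arm is dropped, a modest cost.
- **Arm C.** PC on the oncologist's indication is part of that arm's standard care, and calling it crossover would be wrong. Arm C also has ordinary losses; it lacks only the attendance exclusion.
- **Phase II.** The Discussion ranks statistical significance below the main aims. That tempers the type I error argument but not the bias in the effect size.

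**Conclusion.** The point holds as a defect of the stated rule. Exclusion depends on attendance after randomisation, applies to A and B only, is stricter in A, and is not limited to a secondary analysis. None of the four planned contrasts, nor the interim A versus B effect size, compares the groups as randomised.

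The size is unknown. Over the assumed ranges it runs from negligible (0.025 SD, type I error 5.1%) to serious (0.20 SD, about 31% of the design effect, with type I error about 12% for A versus C and 15% for A+B versus C). These figures rest entirely on the assumed f and g, and on excluded patients faring worse.

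On feasibility, the supported conclusion is narrower than a general overstatement of acceptance. The passages conflict if read literally, and on any reading non-acceptors are absent from the satisfaction and depression comparisons that are primary outcomes.

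**What to change.** Replace the exclusion sentence in Early palliative care and add matching text to Statistical analysis:

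1. The primary between-arm analysis of FAMCARE-Patient, HADS-D and PHQ-9 includes every randomised patient in the assigned arm, with all available post-baseline data. The interim A versus B effect size uses the same population.
2. The scheduled questionnaires continue to be collected from patients who do not attend.
3. Attendance, absences and their reasons are reported with all patients randomised to A and B as denominator.
4. The set defined by attendance is kept only as a labelled sensitivity analysis.

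**Cost.** Questionnaires are already scheduled for all patients, so the change is mainly one of wording, plus the effort of following non-attenders. The real price is possible dilution. If d = 0.65 holds only for attenders and non-attenders gain nothing (an assumption), 20% non-attendance gives 0.65 × 0.80 = 0.52, and power with 37.5 per arm is about 60% instead of 79%. Sample size calculation should therefore say whether 0.65 refers to all randomised patients or to attenders, and whether the 25% to 30% loss includes non-attendance.

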### Primary outcome measures

The primary outcome measures are listed below:Descriptive results about the feasibility of the interventions (the average duration of each intervention session in minutes, the number of absences and the reasons for non-attendance in the intervention groups, the accrual rate, and the reasons for ineligibility).Changes in satisfaction with care from baseline according to the FAMCARE-Patient scale at days 45, 90, 120 and 180.Changes in depression symptoms from baseline according to the HADS-D and PHQ-9 at day 90.

### Secondary outcome measures

The secondary outcome measures are listed below:Changes in depressive symptoms from baseline according to the HADS-D and PHQ-9 at days 45, 120 and 180.Changes in anxiety symptoms from baseline according to the HADS-A at days 45, 90, 120 and 180; the proportion of patients who believe that their cancer is curable as measured using an adapted instrument to evaluate patient awareness (all of the patients will have incurable advanced cancers; therefore, patients who claim that their disease is curable will be interpreted as not being adequately aware of their prognosis).Changes in cancer symptoms from baseline according to the ESAS-br at days 45, 90, 120 and 180; changes in QL from baseline according to the EORTC QLQ-C15-Pal at days 45, 90, 120 and 180.

### Statistical analysis

The demographic and clinical pretreatment characteristics of the patients will be compared between the study arms (A *versus* B *versus* C) using the analysis of variance (ANOVA) test for independent measurements (for the continuous variables) and the chi-squared test (for the categorical variables). Data normality will be assessed using the Shapiro-Wilk test [26] and the data distribution patterns. Cohen’s *d* effect size will be calculated according to the mean difference between the two treatment evaluations divided by the pooled standard deviation of the sample. The analysis of repeated measurements will be performed for each type of outcome at 45, 90, 120 and 180 days after randomization, and these results will be compared to those at the beginning of the study. The effect size will be calculated between Arms A versus C, B versus C, A versus B, and also Arms A plus B versus C. The effect size between the groups will be considered small (0.20 to 0.49), moderate (0.5 to 0.79) or large (≥0.80) [27]. The scores for depression and anxiety symptoms and QL will be compared over time using a mixed model analysis of variance (ANOVA) for repeated measurements. The disease awareness scores and the rate of end-of-life invasive procedures will be compared using the chi-squared test (or Fisher’s exact test). A *P* value <0.05 will be considered statistically significant. The statistical software SPSS v.21 will be used for the statistical analyses.

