## Discussion

The feasibility and impact of a brief psychosocial and educational strategy, which is based on CBT, will be evaluated in patients with advanced cancer who start palliative chemotherapy to determine whether the patients will be in a better condition when assessed for the first time by a PC team. We believe that the benefits of psychological intervention shall be synergistic to secondary emotional benefits from the early integration of PC. Therefore, this study will evaluate a new strategy for the transition into PC. Furthermore, the inclusion of early PC with or without a brief psychosocial and educational strategy will be compared to standard oncological care in a control arm (first-line palliative chemotherapy) in which patients are referred to PC by the attending physician.

Identifying the reasons patients are referred to PC services is essential because of the benefits of early PC in patients with advanced cancer [6-8,29]. Patients are most likely referred to PC too late even at oncology reference centers [9]. Two randomized phase III trials [6,7] found that early PC was associated with lower levels of depression symptoms compared with standard oncologic treatment. This study aims to confirm this benefit and to examine whether the psychosocial and educational strategy can reduce depression symptoms over time. This original approach may be useful in hospitals with settings similar to those at BCH. This large hospital is dedicated exclusively to oncology and has a well-structured PC service; however, this service is associated with significant patient stigmatization. Patients often perceive the PC unit as being exclusively for dying patients, which complicates their acceptance of early referral to PC.

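### For FAMCARE-Patient and ESAS-br, the only comparison the 5% rule can apply to is with baseline; significance for all score outcomes should rest on the between-arm difference in change

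*Protocol article*

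**What the plan says.** All places are in the protocol article.

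- **Baseline comparison.** Statistical analysis plans a repeated-measurements analysis of every type of outcome at the four follow-up visits and adds the instruction "and these results will be compared to those at the beginning of the study". No test is named, and the text does not say whether the comparison is made within each arm.
- **Between-arm contrasts.** Same section: "The effect size will be calculated between Arms A versus C, B versus C, A versus B, and also Arms A plus B versus C". These are graded small, moderate or large; no test is attached.
- **Model.** Same section: scores for depression, anxiety and quality of life "will be compared over time using a mixed model analysis of variance (ANOVA) for repeated measurements". FAMCARE-Patient and ESAS-br are not in that sentence. Disease awareness and end-of-life procedures are assigned a chi-squared or Fisher test.
- **Significance rule.** Stated once for the whole section: a P "value <0.05 will be considered statistically significant".
- **Objective.** For depression, Main objectives asks "to compare the differences between the intervention groups and the control group and between the intervention groups". Secondary objectives sets the same contrasts for anxiety, quality of life and symptom scores.
- **Outcome definition.** Primary outcome measures: "Changes in depression symptoms from baseline according to the HADS-D and PHQ-9 at day 90". Satisfaction on FAMCARE-Patient is also a primary outcome, as change from baseline at four visits.

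**The concern.** The objectives for depression, anxiety, quality of life and symptoms are between-arm, and the sample size is calculated for a difference between independent means. The comparison stated for each type of outcome, however, is with the start of the study. A change from baseline in patients beginning palliative chemotherapy mixes any treatment effect with adjustment, regression to the mean and the course of the disease. A significant change in one arm and a non-significant one in another is not a test of the difference between the arms.

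The gap is widest for FAMCARE-Patient and ESAS-br. An analyst who followed the section as written would have a P value against baseline and a Cohen's d between arms, but no between-arm test. For depression, anxiety and quality of life, the mixed ANOVA could supply the right test through its group-by-time term. The section describes it only as a comparison over time, which its time main effect would also satisfy, and that effect is not a treatment comparison.

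At stake is a report that an outcome improved significantly with early palliative care but not with standard care, when all arms changed alike.

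**Working it through.** **The plan's own figure.** Sample size calculation gives 39 per arm for d = 0.65, two-sided 5%, 80% power, independent means. The exact noncentral-t calculation gives power 79.9% at 38 per arm and 80.9% at 39, so 39 is reproduced. The trial is therefore sized for a between-arm comparison, and this point does not affect that figure.

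**Inputs.** From the document: 39 evaluable per arm; 50 enrolled per arm with 25% to 30% loss, so 50 × 0.70 = 35 to 50 × 0.75 = 37.5 remaining; 5% level. I use 35, 39 and 50. Assumptions: the baseline comparison is a two-sided paired t test in each arm; there is no treatment effect; every arm has the same true change. That change, dz, is the mean change divided by the SD of change. The document gives no value for it, so a range is shown.

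**Formulas.** Let p be the probability that one arm's paired test is significant (noncentral t, n − 1 degrees of freedom, noncentrality dz√n). The arms are independent, so:

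- P(A or B significant, C not) = [1 − (1 − p)²](1 − p)
- P(one named arm significant, C not) = p(1 − p)

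Example, n = 39 and dz = 0.3: p = 0.447, so (1 − 0.553²) × 0.553 = 0.694 × 0.553 = 0.384.

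| dz | p (n = 39) | A or B, not C: n = 35 | n = 39 | n = 50 | One named arm, not C (n = 39) |
|---|---|---|---|---|---|
| 0 | 0.050 | 0.093 | 0.093 | 0.093 | 0.048 |
| 0.1 | 0.093 | 0.154 | 0.161 | 0.180 | 0.085 |
| 0.2 | 0.230 | 0.297 | 0.313 | 0.349 | 0.177 |
| 0.25 | 0.331 | 0.357 | 0.370 | 0.385 | 0.221 |
| 0.3 | 0.447 | 0.384 | 0.384 | 0.360 | 0.247 |
| 0.4 | 0.682 | 0.318 | 0.286 | 0.199 | 0.217 |
| 0.5 | 0.861 | 0.175 | 0.137 | 0.066 | 0.120 |
| 0.65 | 0.977 | 0.038 | 0.023 | 0.005 | 0.023 |

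**Bounds.** With u = 1 − p the first formula is u − u³, largest at u = 1/√3 (p = 0.42), where it equals 0.385. It reaches one third only when p lies between about 0.26 and 0.61. The second formula is at most 0.25, at p = 0.5.

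**Between-arm test.** In 40,000 simulated trials at 39 per arm with no treatment effect, a two-sample test of change (A versus C) rejected in 4.9% to 5.2% at dz = 0, 0.2, 0.3 and 0.4. The pattern of A or B significant and C not occurred in 9.4%, 31.2%, 38.4% and 28.7% of the same trials, matching the formula.

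**Like for like.** Two between-arm contrasts (A–C and B–C), each at 5%, give at least one rejection in at most 0.05 + 0.05 = 10% of trials. With no common change the within-arm pattern, at 9.3%, is therefore no worse. The excess arises only when the arms share a change, and there the between-arm test is unaffected.

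**The case against.** **The sentence need not mean a within-arm test.** It names no paired test and no arm-by-arm analysis, and does not say that conclusions about treatment rest on it. Most score outcomes are defined as change from baseline, so comparing with baseline may only describe how the outcome is formed, or a time factor in a repeated-measures model. This stands: the within-arm reading is an inference, and the rates above are conditional on it.

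**Between-arm comparison is already present.** The objectives, the four effect-size contrasts, the mixed ANOVA and the sample size all point to it. A reader might infer that the plan would hide a benefit if every arm deteriorated; it would not, because the between-arm effect sizes would show it. But an effect size without a test does not tell the analyst what the 5% rule applies to, and FAMCARE-Patient and ESAS-br are outside the ANOVA sentence.

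**Satisfaction has no stated between-arm objective.** Main objectives places it under feasibility. This stands, so FAMCARE-Patient does not contradict its objective. It is still a primary outcome of a randomized trial whose only testable comparison is with baseline. ESAS-br does have a between-arm symptom objective.

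**The article is condensed and the study preliminary.** Naming a model term is often left to the full plan, and the Discussion ranks significance below the study's main aims. This lowers the stakes. The article nonetheless states a comparison and a 5% rule, and depression at day 90 is a main objective.

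**The Discussion.** A reader might cite the aim to "examine whether the psychosocial and educational strategy can reduce depression symptoms over time" as proof of a before-and-after question. It is not: the same part of the Discussion says that both strategies are compared with a standard-care control arm. No change is needed there.

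**Conclusion.** The point holds as a gap in the stated basis for inference. For FAMCARE-Patient and ESAS-br, the baseline comparison is the only one to which the 5% rule can apply. For depression, anxiety and quality of life a suitable model is planned, but its group-by-time contrast is not named as what decides significance.

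If the baseline comparison is tested within arms, A or B is significant and C is not, with no treatment effect, in about 9% of trials per outcome and visit when the arms share no change, up to about 38% with a moderate shared change, and close to 0 with a large one. For one named arm against C the rate is at most 25%. A single between-arm test of change stays at about 5%. The size of the shared change is assumed.

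Two stronger readings are not supported. One is that every outcome is to be tested within arms: the text does not say within arms, and disease awareness and end-of-life procedures have their own tests. The other is that about a third of null trials would mislead: that holds only for a moderate shared change, which the document neither states nor implies.

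**What to change.** In Statistical analysis, replace the comparison with the start of the study by wording such as: For every score outcome, including FAMCARE-Patient and ESAS-br, statistical significance is judged only on the between-arm difference in change from baseline at the stated visit, estimated as the group-by-time contrast from the mixed model. Within-arm change is reported as mean and 95% CI, without P values.

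This brings the analysis into line with the between-arm objectives and with the comparison used for the sample size. The chi-squared and Fisher tests and the effect-size contrasts can stay as they are. The change needs no further data or patients. The downside is fewer significant-looking results to report.
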